### Outcome measures

The primary outcomes will be the “number of new carious surfaces” (∆DMFS) and “gingival bleeding score” (% of surfaces with gingival bleeding), whereas secondary outcomes will be changes in oral health self-efficacy and behaviors (Table 2).

**Table 2 Tab2:** Outcome measures

Outcomes	Variables	Codes	Source of information
Secondary outcomes			
Change in self-efficacy^a^			
Snacking	Views on the statements “I can control snacks to once a day or less when … (under several scenarios)”	(1) Not at all; (2) A little of the time;	Questionnaire
		(3) Sometimes; (4) Most of the time;	
		(5) All the time	
Toothbrushing	Views on the statements “I can brush my teeth twice a day when … (under several scenarios)”	1) Not at all; (2) A little of the time;	Questionnaire
		(3) Sometimes; (4) Most of the time;	
		(5) All the time	
Change in behaviors			
Snacking	Frequency of snacking per day	(1) None; (2) Once; (3) Twice;	Questionnaire
		(4) 3 times; (5) 4 times or more	
Toothbrushing	Frequency of toothbrushing per day	(1) Less than once; (2) Once;	Questionnaire
		(3) Twice; (4) 3 times or more	
Primary outcomes			
Gingival health	Gingival bleeding score (% of tooth surfaces with gingival bleeding)	Continuous	Oral examination
Caries increment	Number of new carious surfaces	Continuous	Oral examination
	Presence/absence of new carious surfaces	Nominal	Oral examination

^a^Six scenarios will be used, namely “when feeling down in the dumps,” “when busy and overloaded,” “when tired,” “when on a vacation,” “when it means stopping doing something that is enjoyable” and “if there is a slip up, will the subject resume controlling”

At baseline and after 6, 12 and 24 months, participants will be examined by a trained dentist calibrated against an experienced oral epidemiologist. The examiner will be blinded to the group allocation of each school. Dental caries will be registered by following the International Caries Detection and Assessment System (ICDAS), which differentiates seven stages of caries development (from sound to early enamel lesion to extensive cavity) [27]. Gingival health will be evaluated using the Gingival Bleeding Index [28]. Participants will be examined in a supine position, with an illuminated mouth mirror and a CPI probe. The tooth status will be assessed by visual inspection, aided by tactile inspection if necessary. Duplicate examinations will be carried out on 10 % of the participants to assess intraexaminer reliability.

Before each oral examination, a questionnaire will be completed by the participants on a self-administered basis to gather information on their sociodemographic background and oral health knowledge, self-efficacy and behaviors. For oral health behaviors, participants will be asked how many times they snack and brush their teeth in a day. Their oral health self-efficacy will be measured by asking the participants whether they can “control snacks to once a day or less” and “brush teeth at least twice a day” under six scenarios, namely “when feeling down in the dumps,” “when busy and overloaded,” “when tired,” “when on a vacation,” “when it means stopping doing something that is enjoyable,” and “if there is a slip up, will the subject resume controlling” [29]. Participants are required to rate their control of oral health behaviors among “not at all,” “a little of the time,” “sometimes,” “most of the time” and “all the time.”

### Statistical analysis

Data will be analyzed using the computer software Statistical Package for Social Sciences (SPSS). Effectiveness of the intervention schemes over 6, 12 and 24 months will be evaluated on an intention-to-treat basis. All participants randomly assigned to each group will be included in the analysis, regardless of whether they receive the intervention or complete the study. If a participant is lost to follow-up, the last known outcome status will be carried forward.

Chi-square tests will be used for comparing distributions, whereas parametric or nonparametric methods, as appropriate, will be adopted for comparing means. Effect sizes (relative risk) and their 95 % confidence intervals (95 % CI) will be calculated and reported with *P* values. Multivariate analysis, namely ANCOVA (analysis of covariance) and multiple regressions, will be performed to evaluate the effects of various factors (intervention, school, counselor, participant’s sex, socioeconomic background and baseline caries experience) on the outcomes.

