## Methods/Design

### Sample size calculation

The primary outcomes of this study are the “number of new carious surfaces” (∆DMFS) and “gingival bleeding score” (% of surfaces with gingival bleeding). An effect size of 0.4 (based on means) is considered clinically significant for both variable [24]. Based on a significance level of 5 % and a targeted statistical power of 80 %, 132 participants in each group will be required. Allowing for a 20 % attrition rate, 165 participants would need to be recruited into each of the three study groups. The total sample size will be 495.

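### Carrying the last status forward on an accruing caries increment understates 24-month caries in any arm with dropout, and distorts the arm difference when there is a true effect or unequal loss

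*Protocol article*

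**What the plan says.** All references are to the protocol article.

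- **Statistical analysis.** The analysis is by intention to treat: "All participants randomly assigned to each group will be included in the analysis, regardless of whether they receive the intervention or complete the study". The only missing-data rule follows: "If a participant is lost to follow-up, the last known outcome status will be carried forward". It applies to every outcome, with no exception for caries.
- **Outcome measures.** "The primary outcomes will be the “number of new carious surfaces” (∆DMFS) and “gingival bleeding score” (% of surfaces with gingival bleeding"). Table 2 adds a binary form of the caries outcome: "Presence/absence of new carious surfaces". On timing: "At baseline and after 6, 12 and 24 months, participants will be examined by a trained dentist".
- **Sample size calculation.** The target is 132 per group. After a 20 % allowance for attrition, "165 participants would need to be recruited into each of the three study groups".
- **Oral health behavioral interventions (Table 1) and Discussion.** Pupils in both motivational interviewing (MI) arms receive five telephone calls over 6 months. Health education (HE) pupils receive none.

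**The concern.** An increment counted from baseline is 0 at baseline by definition and builds up with time at risk. Carrying an earlier value to 24 months amounts to saying that no further surface became carious after the pupil was last seen. A pupil never re-examined has baseline as the last known status, so is scored 0 new surfaces, the best possible result, and counted as caries-free on the binary version. A pupil last seen at 6 or 12 months contributes 6 or 12 months of disease as if it were 24.

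Two things are at stake. The caries increments reported for each arm would be too low. The comparison between arms could also be distorted, by an amount that depends on how many pupils each arm loses and when. The imputed scores would then be analysed as if they had been observed.

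**Working it through.** **Inputs from the article:** 20 % attrition; 132 per group inflated to 165; standardised effect 0.4; 80 % power; 5 % significance; visits at baseline, 6, 12 and 24 months.

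**Assumptions not in the article:** caries accrues linearly; dropout is independent of outcome; timing of loss is as given in each scenario; the ratio of SD to mean lies between 1 and 2; no school clustering.

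**1. The plan's own figures.** n = 2(z₁₋α/₂ + z₀.₈₀)² / 0.4². At two-sided α = 0.05 this gives 99. At α = 0.05/3 it gives 131 (133 with the t distribution), close to the stated 132. The article does not state that split, and 90 % power at α = 0.05 also gives 132. Then 132 / 0.8 = 165 and 3 × 165 = 495, as stated. The expected loss is 165 − 132 = 33 pupils per arm.

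**2. Arm mean under carry-forward.** Let d be the share lost and f the average share of the 24-month increment already seen at the last visit (0 at baseline, 0.25 at 6 months, 0.5 at 12 months). The expected mean is μ × [1 − d(1 − f)].

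| Timing of the 20 % loss | f | Share of true mean |
|---|---|---|
| All before 6 months | 0 | 1 − 0.2 × 1 = 0.80 |
| Even over three intervals | (0 + 0.25 + 0.5)/3 = 0.25 | 1 − 0.2 × 0.75 = 0.85 |
| All after 12 months | 0.5 | 1 − 0.2 × 0.5 = 0.90 |

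In pupils, for even loss: (132 × 1 + 11 × 0 + 11 × 0.25 + 11 × 0.5) / 165 = 140.25 / 165 = 0.85.

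**3. Equal loss in both arms.** Both means are multiplied by the same factor. The absolute difference therefore shrinks by 10-20 %, the ratio of means is unchanged, and a true difference of zero stays zero. In simulation (negative binomial counts, mean 1-2 surfaces, 165 per arm, even timing), type I error was about 5 %.

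**4. Standardised effect, equal loss.** Take a true effect of 0.40 SD with all loss before 6 months. The difference is 0.8 × 0.4 × SD, and each arm's variance is 0.8(SD² + μ²) − (0.8μ)², using that arm's own mean.

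- SD/mean = 1 (means 1 and 0.6, SD 1): variances 0.96 and 0.8576, average 0.9088. Effect = 0.32 / √0.9088 = 0.336.
- SD/mean = 2 (means 1 and 0.2, SD 2): variances 3.36 and 3.2064, average 3.2832. Effect = 0.64 / √3.2832 = 0.353.

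With even loss the effect is 0.355-0.372 SD, depending on how partial increments vary.

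**5. Unequal loss, no true effect.** Illustrative split of 25 % versus 15 %:

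- Even timing: (1 − 0.25 × 0.75) / (1 − 0.15 × 0.75) = 0.8125 / 0.8875 = 0.915, a spurious 8 % reduction.
- All early: 0.75 / 0.85 = 0.882, a spurious 12 % reduction.
- All after 12 months: 0.875 / 0.925 = 0.946, a spurious 5 % reduction.

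Each favours the arm losing more pupils. In a wider split of 30 % versus 10 % with even timing, simulated type I error was about 13-23 % at a nominal 5 %. Analysing completers only stayed near 5 % under the same dropout assumption.

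**6. Unequal loss with a true effect.** In one simulated scenario the true difference was 0.98 surfaces. With 30 % lost in the control arm and 10 % in the better arm, the estimate fell to 0.61. With the losses reversed, it rose to 1.06.

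**The case against.** Several stronger readings are tempting, and the article does not support them.

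- **That carry-forward always biases the arm comparison, or always dilutes it.** It does not. With equal loss and no true effect the difference is unbiased. With equal loss and timing the ratio of means is preserved. With heavier loss in the better arm the difference grows.
- **That pupils look healthier on both primary outcomes.** Gingival bleeding is a current percentage of surfaces, not an accruing count. A carried baseline value flatters an arm if bleeding worsens and penalises it if bleeding improves.
- **That a 0.40 SD effect is cut to 0.34-0.35 SD.** That needs every dropout to leave before 6 months.
- **That power collapses.** At α = 0.05/3, 132 completers at 0.40 SD give 80.4 %. Carry-forward on 165 gives about 80-84 % with even loss and 74-79 % with all-early loss, so the deficit runs from none to about 6 points.
- **That unequal dropout is documented.** No rates by arm are given. The calls end at 6 months, their stated goals concern behaviour change rather than attendance, and the examination schedule is common to all arms. If HE did lose more pupils, the caries bias would favour HE and make an MI benefit harder to show. The spurious gap at 25 % versus 15 % (even to early loss) is 0.075-0.10 of the mean, or about 0.04-0.10 SD, against a threshold of 0.4.

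The article also names no single primary time point, and the figures above describe 24 months, where carry-forward does most harm. Some early lesions may reverse, which softens the assumption of steady accrual without removing the problem.

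All of this limits the size and direction of the effect on comparisons. None of it rescues the understated arm means. An unseen analysis plan might add supplementary analyses, but the article commits to carry-forward explicitly, so the fault is in a stated rule and is not an omission. Intention to treat does not require the rule either: imputation and likelihood-based models can also retain randomised pupils.

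**Conclusion.** The point holds for the caries increment and its presence/absence version. At the planned 20 % attrition, carry-forward understates each arm's 24-month mean increment by 10-20 %, with 15 % for evenly spread loss. The absolute difference shrinks by the same share when loss is equal and a true effect exists. When loss differs between arms, the comparison moves in favour of the arm losing more pupils, by 8-12 % in relative terms for 25 % versus 15 % loss (even to early timing) and no true effect. Because the direction depends on which arm loses more, the rule cannot be defended as conservative.

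These sizes rest on linear accrual, on dropout independent of outcome, and on assumed timing and splits of loss. Unequal loss is possible, given calls in the MI arms only, but the article does not quantify it. For gingival bleeding the conclusion is weaker: the carried value is out of date, possibly from before the intervention, and the direction of bias is open.

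**What to change.** Remove carry-forward as the primary method and state a replacement for each primary outcome.

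- **Caries increment and its binary version:** multiple imputation with arm, school, baseline and earlier visits in the imputation model. For the count, an alternative is a count model that uses all observed visits and takes follow-up time into account.
- **Gingival bleeding:** a likelihood-based repeated-measures model on all observed visits, or the same imputation.
- **Sensitivity analyses:** keep carry-forward here if it is wanted, and add an analysis for data missing not at random, since the primary analysis would then rest on a missing-at-random assumption.
- **Reporting:** give the number lost and the last visit attended by arm, so that readers can judge any imbalance.

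The cost is analysis wording, modest programming and reliance on that missing-at-random assumption. No new data are needed and the sample size does not change. The Trial status section says recruitment has not begun, so the change can be made before any outcome is seen.

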### Participant recruitment and randomization

CONSORT guidelines [25] will be followed in the design, implementation and reporting of this randomized controlled trial. The protocol of this study was reviewed, and ethical approval was granted by the institutional review board of the University of Hong Kong and the Hospital Authority Hong Kong West Cluster (IRB #UW14-142).

To be eligible to join this study, a participant should (a) be a Form-1 or Form-2 student (aged 12 to 13 years) in a participating school, (b) have unfavorable oral health behavior(s) (that is, be a student who needs intervention), and (c) have Internet access via computers or mobile devices (smart phone, iPad etc.). Unfavorable oral health behaviors are defined as “snacking twice or more a day” and/or “brushing teeth less than twice a day.” A student will be excluded if he/she (i) is unable to cooperate in the related procedures due to severe health conditions, (ii) cannot speak Cantonese or (iii) cannot read and type Chinese.

This study will be conducted in nine secondary schools; three in each of Hong Kong’s three main districts (Hong Kong Island, Kowloon and the New Territories). All schools are co-ed schools, both sexes are included, and there is a balance in sexes across groups. The three schools in each district will be randomly allocated by the drawing of lots in sealed envelopes to one of three groups: (1) HE, (2) face-to-face MI or (3) online group MI. The group allocation will be done by a researcher not involved in delivering the intervention and assessing the outcomes.

All Form-1 and Form-2 students in the participating schools will be approached. Parental written consent and student’s assent will be obtained on their participation. Eligible participants will be identified through a standardized questionnaire on students’ demographic information, current snacking and toothbrushing habits, access to the Internet and language proficiency. The recruitment process will be monitored to ensure the characteristics of participants across the three groups are balanced with regard to their socio-demographic profile (sex and parental education level) and baseline behaviors (snacking and brushing). In the three schools allocated to each intervention group, 165 participants will be recruited; 55 from each school. The total number of participants will be 495 for the whole study.

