## Discussion

To the best of our knowledge, this study is the first attempt to introduce other mode of MI delivery, besides face-to-face individual counseling, into dental interventions. It taps into an unexplored area and is likely to generate useful evidence. Since online group MI is expected to be more convenient, accessible, and time efficient, it might address the practicality issues and pave the way for the application of MI in dental practice. The inclusion of online interventions into this study is also in line with the trend of Telehealth, in which information and communication technology is incorporated into health care delivery and is transforming the practice in many areas [30].

In this trial, randomization will be carried out at school level, instead of at individual level. Students in each participating school will receive the same intervention. This is to avoid intervention contamination, which is likely to happen if students in the same school are assigned to different groups. By randomly assigning the three schools from each district into three different groups and by monitoring the recruitment process, a balance will be reached in the characteristics of participants in the different groups with regard to their sociodemographic background and baseline behaviors. Since MI can rarely be completed in a single contact, follow-up phone calls will be made after the counseling session to assist the start of changes, explore solutions to the problems encountered, promote maintenance, avoid relapse and help re-establish change. Follow-up phone calls will not, however, be made in the HE group, so that the intervention reflects precisely the prevailing health education practice. The outcomes of the interventions will be evaluated by using psychological, behavioral and clinical measures at three points of time. This will allow us to interpret the results in a more complete manner.

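### Schools are randomised, but the between-arm tests named in the Statistical analysis section carry no stated allowance for school clustering, so their P values and intervals are too optimistic if the ICC is positive

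*Protocol article*

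**What the plan says.** The unit of randomisation is explicit. The Discussion states: "In this trial, randomization will be carried out at school level, instead of at individual level". Under Participant recruitment and randomization: "This study will be conducted in nine secondary schools; three in each of Hong Kong’s three main districts", and "The three schools in each district will be randomly allocated by the drawing of lots in sealed envelopes to one of three groups". Each arm therefore has three schools, one per district. Cluster size is also fixed: "In the three schools allocated to each intervention group, 165 participants will be recruited; 55 from each school".

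For between-arm comparisons, the Statistical analysis section states: "Chi-square tests will be used for comparing distributions, whereas parametric or nonparametric methods, as appropriate, will be adopted for comparing means". It also plans relative risks with 95 % confidence intervals and P values. It then plans ANCOVA and multiple regressions with a list of factors that includes intervention, school and counselor. Participants lost to follow-up stay in the analysis through carry-forward of their last status. The section names no mixed model, GEE, cluster-robust standard error or school-level analysis.

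**The concern.** In their usual form, chi-square tests, two-sample or rank comparisons and relative-risk intervals treat every pupil as an independent observation. Here an arm holds up to 165 pupils but only three independently allocated units. If pupils in one school resemble each other more than pupils in different schools, these methods understate the standard error of an arm difference. Between-school variation can then pass for an effect of motivational interviewing, and the intervals are too narrow. Both primary outcomes (new carious surfaces and gingival bleeding score) are exposed to this.

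**Working it through.** **Inputs from the protocol article.** Three schools per arm; 55 pupils per school; 20 % attrition, so 55 × 0.8 = 44 completers per school; effect size 0.4 SD; 5 % significance; 80 % power; 132 per group. **Assumed.** Two-sided tests (sidedness is not stated) and ICC values of 0.01, 0.02 and 0.05 (the documents give none).

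**The plan's own figure.** The Sample size calculation says: "Based on a significance level of 5 % and a targeted statistical power of 80 %, 132 participants in each group will be required". For independent pupils, n = 2(z₁₋α/₂ + z₁₋β)²/0.4². At two-sided 5 % and 80 % power this gives 99 (exact t: 100). With α divided by three, for three pairwise comparisons, it gives 131 (exact t: 133), close to 132. At 5 % and 90 % power it gives 132, but the article states 80 %. Attrition checks: 132/0.8 = 165. All of these are formulas for individually randomised pupils. The excess of 132 over 99 would act as a design effect only at an ICC of (132/99 − 1)/43 ≈ 0.008, and the article does not present it as one.

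**Error of the pupil-level test.** Design effect DE = 1 + (m − 1) × ICC. True type I error of a nominal 5 % test = 2 × [1 − Φ(1.96/√DE)]. Standard errors are understated by √DE. All between-school variance is taken here to lie within districts.

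| ICC | DE, m = 44 | √DE | Type I error | DE, m = 55 | √DE | Type I error |
|---|---|---|---|---|---|---|
| 0.01 | 1.43 | 1.20 | 10.1 % | 1.54 | 1.24 | 11.4 % |
| 0.02 | 1.86 | 1.36 | 15.1 % | 2.08 | 1.44 | 17.4 % |
| 0.05 | 3.15 | 1.77 | 26.9 % | 3.70 | 1.92 | 30.8 % |

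The m = 55 columns apply if carry-forward keeps everyone in. At 44 per school, a nominal 95 % interval covers about 90 %, 85 % and 73 %.

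**Simulation** (8,000 runs, three against three schools, m = 44). The t test rejected in 10.0 %, 15.7 % and 27.6 % of runs and the chi-square test in 9.8 %, 14.9 % and 28.0 %. A t test on school means rejected in 4.9 %, 5.2 % and 4.7 %.

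**District stratification.** Each arm has one school per district, so district variance cancels from the arm contrast. Suppose half of a total between-school ICC lies between districts. The contrast variance relative to the naive one is then 44 × ICC/2 + (1 − ICC) = 1.21, 1.42 and 2.05, and type I error is about 7.5 %, 10 % and 17 % at 44 per school.

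**School as a fixed factor.** With nine schools and one arm per school, the design matrix of school indicators has rank 9. Adding the three arm indicators leaves it at rank 9. The arm effect is then not separately estimable.

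**Power of a valid analysis.** SE = √(2 × DE/132) = 0.147, 0.168 and 0.218 SD. Noncentrality 0.4/SE = 2.72, 2.38 and 1.83. On 6 df (nine schools minus three arms; critical t 2.45), power is about 62 %, 52 % and 34 %. On 4 df (district block; critical t 2.78), with the same variance, it is about 54 %, 44 % and 29 %. The 95 % half-width on 6 df is 0.36, 0.41 and 0.53 SD, against 1.96 × √(2/132) = 0.24 SD for the naive interval.

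**The case against.** The strongest objection is that school is in the plan, as a factor in the ANCOVA and regressions. A reader might infer that nothing in the plan brings school into the analysis at all, and the text does not support that. It leaves open whether school is fixed or random. A random school effect nested in arm would put school variance into the error term. This part of the objection stands. It does not rescue the plan, because no random effect is stated, a fixed factor is aliased with arm, and the chi-square tests, comparisons of means and relative risks are untouched either way.

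Second, the sentence on tests is generic. It assigns no test to a given outcome and does not say which analysis is confirmatory, and a fuller plan may exist. So it cannot be said that every comparison will be wrong by a known amount. Still, the article does name its methods, and as named they do not match its own unit of randomisation. That is more than a detail left to another document.

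Third, a reader might take "All participants randomly assigned to each group will be included in the analysis" as a claim that pupils were individually randomised. It is ordinary intention-to-treat wording, and school-level allocation is stated plainly elsewhere. It is not evidence for this point.

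Fourth, the size rests on assumed ICCs, and stratifying by district removes some of the variance. Both are right. They change the amount of the error, but not its direction for any positive within-district ICC.

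**Conclusion.** The point holds in this form: the named between-arm tests do not allow for the school-level randomisation, and listing school as a factor with no stated role does not correct them. With assumed ICCs of 0.01 to 0.05, true type I error is about 10 % to 27 % at 44 pupils per school, or 11 % to 31 % at 55. It falls to about 7.5 % to 17 % (44 per school) if half the between-school variance lies between districts. These are conditional figures, not estimates for this trial. They leave out any further correlation within the online counselling groups of six to eight.

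A reader might also infer that only the analysis wording needs to change. The power figures do not support that: a valid analysis of three schools per arm falls well short of the stated 80 % for 0.4 SD across this range.

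**What to change.** For between-arm comparisons, replace the pupil-level tests with one of:

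- a mixed model with a random intercept for school and Satterthwaite or Kenward-Roger degrees of freedom; or
- a two-stage analysis of covariate-adjusted school means (or school proportions for binary outcomes), with a t reference on the between-school df: 6, or 4 with district as a block.

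Do not enter school as a fixed factor beside arm, and do not rely on large-sample sandwich errors with nine schools. Report the observed ICC for each primary outcome. The Trial status section says recruitment has not started, so this can be settled before any data exist.

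The cost is wider intervals and the lower power shown above. The district block takes 2 df and lowers power further unless districts differ enough to repay it. The blocked analysis was not simulated here. The protocol should state openly that power under a valid analysis is below 80 %.

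### The adjusted model lists intervention and school together as factors although each school has one intervention, so intervention has no degrees of freedom if both are fitted as ordinary factors

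*Protocol article*

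**What the plan says.** All references are to the protocol article.

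- **Statistical analysis**, on the adjusted comparison: "Multivariate analysis, namely ANCOVA (analysis of covariance) and multiple regressions, will be performed". Its purpose is "to evaluate the effects of various factors (intervention, school, counselor", followed by sex, socioeconomic background and baseline caries experience. School stands in the same list as intervention and the pupil covariates.
- **Participant recruitment and randomization**: "This study will be conducted in nine secondary schools; three in each of Hong Kong’s three main districts". Then: "The three schools in each district will be randomly allocated by the drawing of lots in sealed envelopes to one of three groups". Each arm therefore holds three schools, one from each district, and "165 participants will be recruited; 55 from each school".
- **Discussion**: "randomization will be carried out at school level, instead of at individual level", and "Students in each participating school will receive the same intervention".

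Nowhere does the article call school a random effect, a nested factor or a clustering unit. It also does not say that school and intervention go into separate models.

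**The concern.** School is nested in intervention: once a pupil's school is known, so is the arm. An ordinary ANCOVA or regression that adjusts for school as a factor removes all differences between schools, and in this design the arm differences are differences between schools. Nothing is left from which to estimate intervention.

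At stake is the planned adjusted comparison of health education, individual MI and online group MI, in the only analysis that names the randomised unit. One outcome is visible: an empty line for intervention. The other is easy to miss: the software deletes redundant columns and prints an intervention coefficient with a P value, and a reader takes it for the treatment effect. The mention of school could also be taken as evidence that clustering has been handled. Entered in this way, it has not.

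**Working it through.** **Inputs.** From the article: 9 schools, 3 arms, 3 schools per arm, 55 pupils per school, 20% attrition, and an effect of 0.4 ("An effect size of 0.4 (based on means) is considered clinically significant"). Assumed: two-sided 5% tests, and ICCs of 0.01 to 0.10, because the article gives no ICC.

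**The plan's own counts.** 132 / (1 − 0.20) = 165 per arm; 3 × 165 = 9 × 55 = 495. These agree. After 20% loss, a school has 55 × 0.80 = 44 pupils. This point disputes none of these figures.

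**Step 1: rank.**

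| Fixed terms | Columns | Rank |
|---|---|---|
| Intercept + school | 1 + 8 = 9 | 9 |
| Intercept + school + intervention | 9 + 2 = 11 | 9 |
| Intercept + school + 3 pupil covariates + counselor | 13 | 13 |
| The same + intervention | 15 | 13 |

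Degrees of freedom for intervention given school: 9 − 9 = 0, and 13 − 13 = 0 with the covariates. The arm contrast is not estimable in either model. This depends on neither sample size nor ICC.

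**Step 2: what a printed coefficient would mean.** With reference-level coding, dropping redundant columns leaves a contrast between one reference school in each arm. Take total variance 1, ICC ρ and m pupils per school.

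- Variance the model reports: 2(1 − ρ)/m
- True variance under no treatment effect: 2[ρ + (1 − ρ)/m]
- False-positive rate: 2[1 − Φ(1.96 × √(reported/true))]

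For m = 55:

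| ρ (assumed) | Reported | True | 1.96 × √ratio | False-positive rate |
|---|---|---|---|---|
| 0.01 | 0.0360 | 0.0560 | 1.57 | 12% |
| 0.02 | 0.0356 | 0.0756 | 1.35 | 18% |
| 0.05 | 0.0345 | 0.1345 | 0.99 | 32% |
| 0.10 | 0.0327 | 0.2327 | 0.73 | 46% |

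With m = 44 the rates are 10%, 15%, 28% and 42%. Constraining school effects to sum to zero within each arm averages three schools per arm. Both variances are then divided by 3, so the ratio and the error rates are essentially unchanged.

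**Step 3: school as the random unit.** Intervention is tested on 9 − 3 = 6 df. With district fitted, 9 − 3 − 2 = 4 df remain; intercept, intervention and district give 5 columns of rank 5, so district causes no aliasing. In a simulation of 20,000 runs, a school-level test on 6 df rejected a true null in 4.8% to 5.1% of runs.

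**Step 4: power after the repair.** For a difference d = 0.4 between two arms:

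- Standard error = √(2[1 + (m − 1)ρ]/(3m))
- Power from the noncentral t with noncentrality 0.4/SE

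For m = 44 and ρ = 0.05: design effect 1 + 43 × 0.05 = 3.15; SE = √(2 × 3.15/132) = 0.218; noncentrality 0.4/0.218 = 1.83; critical t on 6 df = 2.447; power 34%.

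| ρ (assumed) | Power, 6 df | Power, 4 df |
|---|---|---|
| 0.01 | 62% | 54% |
| 0.05 | 34% | 29% |
| 0.10 | 22% | 20% |

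The 4-df column gives district no credit for explaining variation between schools, so it is the pessimistic end.

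**The case against.** **School may have been meant as random.** The article never says fixed, a factor in ANCOVA can be either, and a nested ANCOVA with school random is standard for this design. On that reading intervention is estimable on 6 df. This stands as a limit: non-estimability is conditional on fitting school as an ordinary factor. It does not clear the wording, because the article names only ANCOVA and multiple regressions and lists school beside sex and baseline caries with no sign of different treatment. This is more than detail left to a fuller document, since the stated factor list conflicts with the stated allocation.

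**The factors may enter separate models.** The plural regressions leave room for this, and no formula is given. One joint model is the natural reading, not the only one. If school is left out of the intervention model, the aliasing disappears but the pupil-level test ignores the randomised unit.

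**The damage is limited and overlaps with clustering.** Both parts are fair. The adjusted analysis is not named as primary, and the unadjusted comparisons can still be computed. Their neglect of clustering is a separate, related point that the same repair to the model would help to answer.

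**Stronger readings.** A reader might infer that the trial cannot estimate its treatment effect at all, or that its results will carry a 12% to 46% error rate. The article supports neither. The first ignores the unadjusted analyses and the simple repair. The second requires the software to drop columns and the analyst to take the leftover coefficient as the effect; if intervention simply shows 0 df, no false positive arises. Nor should the power of a 55-against-55 school contrast be set against the stated 80%. At two-sided 5%, 132 per group gives about 90% for an effect of 0.4, and matches 80% only at an unstated level near 0.05/3, so the comparison is not like for like.

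**Conclusion.** Wrong as written, for the adjusted model only. Given one intervention per school, fitting intervention and school as ordinary factors in one model leaves intervention with 0 df. That is exact and needs no outside figure; it rests on two readings, that school is fixed and that the factors share a model. Both are the plain reading of the section, but neither is stated in so many words. The false-positive range of 12% to 46% is a further conditional result. It rests on assumed ICCs of 0.01 to 0.10, 55 pupils per school, and misuse of a coefficient left after redundant columns are dropped.

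**What to change.** Remove school from the list of ordinary factors and state its role, in one of two ways:

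1. School enters as a random effect nested within intervention (for example a random intercept in SPSS MIXED), with Satterthwaite or Kenward-Roger degrees of freedom.
2. Covariate-adjusted school means are analysed, nine values in all.

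Keep intervention, sex, socioeconomic background and baseline status as fixed effects. Say whether district, the randomisation stratum, is a fixed term: intervention is tested on 6 df without it and 4 df with it.

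The change to the text is a sentence or two, with no new data or software. The Trial status section says that recruitment has not begun, so it can be made before any outcome is seen. The real cost is precision. Intervals will be wider, and power for an effect of 0.4 may fall well short of what the pupil-level calculation implies (about 62% to 22% on 6 df with 44 pupils per school, over assumed ICCs of 0.01 to 0.10). That follows from having nine schools and is not caused by the corrected model. The plan should state it openly, with the ICC it assumes.
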